### Sample size and power

The target sample size of 150 neonates is indicated on a power analysis of the hypothesized association between the BPSN and GAs at baseline. This analysis is based on the data from a descriptive-explorative analysis (*n* = 23) and a previous study (*n* = 71; [69]), i.e., assuming an alpha of 0.05, a beta of 0.80, with at least three baseline heel sticks conducted per study infant (taking into account both intra- and inter-infant variability). Because an attrition rate of 10–15% is anticipated, approximately 170 infants will be enrolled in the study.

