**Methods and design:**

This prospective multisite validation study with a repeated measures design will take place in three university hospital neonatal intensive care units (NICUs) in Switzerland (Bern, Basel and Zurich). To examine the impact of GA on pain responses and their variability, the infants will be stratified into six GA groups ranging from 24 0/7 to 42 0/7. Among preterm infants, 2–5 routine capillary heel sticks within the first 14 days of life, and among full-term infants, two heel sticks during the first days of life will be documented. For each heel stick, measurements will be video recorded for each of three phases: baseline, heel stick, and recovery. The infants’ pain responses will be rated according to the BPSN by five nurses who are blinded as to the number of each heel stick and as to the measurement phases. Individual contextual factors of interest will be extracted from patient charts.

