### Study aims

The aim of this observation study is the validation of the BPSN, using a large sample of neonates spanning a full range of GAs. The validation will involve the detection of the underlying structure of the data and the examination of the concurrent validity of the BPSN with the Premature Infant Pain Profile-Revised (PIPP-R; [26]), construct validity, interrater reliability, specificity and sensitivity. Furthermore, the variability of pain reactions over time related to behavioral and physiological patterns will be analyzed and the relationship between behavioral and physiological indicators examined. In addition, the influence of contextual factors on the variability of pain reactions across GA groups will be explored. Finally, the results of this analysis will be used for modification of the BPSN, to account for individual contextual factors in future clinical pain assessment in neonates.

Based on a previous validation study of the BPSN [41], we hypothesize that the BPSN will be a valid and reliable pain assessment tool for premature and term infants. In addition, we expect that the impact of single contextual factors on infants’ pain reaction will be described and considered for future pain assessment. In particular, we anticipate finding a difference in pain reaction depending on GA. Moreover, we hypothesize that behavioral and physiological indicators will show low association across time and that this low association may be explained by the influence of individual contextual factors.

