### Inclusion and exclusion criteria

Premature infants born between 24 0/7 and 36 6/7 weeks of gestation will be included if they are expected to undergo 2–5 routine capillary heel sticks during the first 14 days of life. Full-term infants born between 37 0/7 and 42 0/7 weeks of gestation will be included if they are expected to have at least 2 routine capillary blood samplings during their first days of life. Furthermore, signed consent is needed from the infant’s parents, who have to understand either German or French.

Infants will be excluded if they have suffered a high-grade intraventricular hemorrhage (grades III and IV), if they have a severe life-threatening malformation or suffer from any condition involving partial or total loss of sensitivity, if they have had an arterial cord pH < 7.15, if they have had surgery for any reason, or if they have a congenital malformation affecting brain circulation and/or cardiovascular system. Infants treated with continuous positive airway pressure (CPAP) or mechanical ventilation will be included if they meet the other inclusion and exclusion criteria.

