After written consent has been received, the neonate will be videotaped (using a HC-V757 high-definition camcorder manufactured by Panasonic, Osaka, Japan) during his or her next 2–5 routine capillary heel sticks. Before each heel stick procedure, every infant will receive a dose of 24% oral sucrose (0.2 ml/kg bodyweight) as a pain relieving intervention in accordance with standards of care [66]. Video sequences and physiological variables will be recorded continuously from 2 to 3 min before the beginning of the heel stick procedure (baseline phase), through the heel stick (heel stick phase) and until 2–3 min after the heel stick (recovery phase). Therefore, three rating sequences will be produced for each heel stick. The camera operator will begin each video sequence by focusing on the face of the neonate for at least one minute to allow adequate assessment of facial activity and cry. Then, the infant’s body will be recorded for another minute. For healthy-term infants, six video sequences per infant will be produced, resulting in 96 videos (2 heel sticks * 3 phases * 16 n). For premature neonates, 2010 video sequences (5 heel sticks * 3 phases * 134 n) will be produced. This will lead to a total of 2106 video sequences, all of which will be filmed by trained study collaborators. Each video sequence will be checked for quality, and digitally elaborated by trained study assistants using Final Cut Pro X (Apple Inc., Cupertino, CA, USA) video editing software. To preserve rater blindness, any information that could indicate the heel stick phase to the raters will be eliminated. Data quality and completeness of the video sequences will be controlled continuously by the doctoral student before uploading each video sequence onto a web-based rating tool. The web-based rating tool has been developed specially for the study and includes a randomizing generator. Uploaded sequences are randomized related to sequence number, phases and presentation order. Five trained nurses who are presently working in a NICU and are experienced users of the BPSN will retrieve the randomized sequences from the web-based platform and will rate the behavioral pain reaction by means of the BPSN and the PIPP-R.

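### The sample-size paragraph assumes at least three heel sticks per infant, which the design does not provide, and prints beta where power must be meant; a power shortfall is possible but not shown

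*Protocol article*

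**What the plan says.** Sample size and power: the target of 150 rests on the association between the BPSN and gestational age (GA) at baseline, "assuming an alpha of 0.05, a beta of 0.80", and "with at least three baseline heel sticks conducted per study infant". Pilot data (n = 23) and a previous study (n = 71) are named as the source. About 170 infants are to be enrolled to cover 10–15% attrition.

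Other sections give different numbers of heel sticks:

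- Abstract, Methods and design: "among full-term infants, two heel sticks during the first days of life will be documented".
- Inclusion and exclusion criteria: preterm infants are "included if they are expected to undergo 2–5 routine capillary heel sticks during the first 14 days of life". Term infants need at least two expected samplings.
- Recruitment and data collection procedures: two to five heel sticks are to be filmed per infant. The clip count then uses two for each of 16 term infants (96 clips) and five for each preterm infant: "2010 video sequences (5 heel sticks * 3 phases * 134 n) will be produced". The stated total is 2106.

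Study aims gives the related hypothesis: "we anticipate finding a difference in pain reaction depending on GA".

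**The concern.** The only paragraph that justifies the sample size uses a number of measurements per infant that the rest of the article does not support. Three is more than the two planned for every term infant, more than the two permitted for a preterm infant, and fewer than the five counted for every preterm infant.

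The term infants matter because they sit at the far end of the GA range. They are 16 of 150 (11%), but with equal counts and GA spread evenly within the three bands they hold about 49% of the information on a GA slope. The shortfall from three therefore falls on the infants with the most weight per head.

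The beta label adds to the problem. Beta is the type II error rate, so 0.80 as printed is 20% power. A reader facing a null GA result could not tell from this paragraph what power to judge it against.

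The word baseline is also unclear. Under Recruitment and data collection procedures it is the phase before the stick, whereas the hypothesis concerns the reaction to pain. In the sample-size paragraph it could mean that phase or the first heel-stick occasions.

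**Working it through.** **1. Can the figure of 150 be reproduced?** No. The article gives alpha 0.05 but no sidedness, effect size, variance or within-infant correlation. What can be tested is how far power moves when the three-stick premise is replaced by the counts stated elsewhere.

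**2. The figures that can be checked**

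- Clips: 2 × 3 × 16 = 96; 5 × 3 × 134 = 2010; 96 + 2010 = 2106. The sums agree.
- Mean heel sticks per infant in that count: (2 × 16 + 5 × 134)/150 = 702/150 = 4.68.
- Minimum under the two-to-five rule: 2 × 3 × 134 + 96 = 804 + 96 = 900 clips.
- Enrolment: 150/0.90 = 167 and 150/0.85 = 177. A figure of 170 implies 1 − 150/170 = 11.8% attrition, which is inside the stated range.
- Beta: power = 1 − beta = 1 − 0.80 = 0.20 as printed.

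**3. Inputs for the sensitivity check**

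- From the article: 102 infants at 24 0/7 to 29 6/7 weeks and 48 at 30 0/7 to 42 0/7 weeks, of whom 16 are term, leaving 32 at 30 0/7 to 36 6/7 weeks.
- Assumed: two-sided alpha 0.05; GA evenly spread within each band; a linear GA effect; 80% power when all 150 infants have three measurements; within-infant correlation ρ from 0.1 to 0.9.

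**4. Formulas**

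- The weight of an infant with m measurements is w = 1/(ρ + (1 − ρ)/m).
- The information on the GA slope is Σ w(x − x̄)², where x is GA and x̄ is its weighted mean. R is this quantity divided by its value with m = 3 for all.
- Power = Φ((1.960 + 0.842)√R − 1.960).

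For example, take all infants with two sticks and ρ = 0.1. The weights are equal, so R = (0.1 + 0.9/3)/(0.1 + 0.9/2) = 0.400/0.550 = 0.727. Power = Φ(2.802 × 0.853 − 1.960) = Φ(0.429) = 0.666.

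**5. Results (power)**

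| ρ | preterm 5, term 2 | preterm 4, term 2 | preterm 3, term 2 | all 2 |
|---|---|---|---|---|
| 0.1 | 0.824 | 0.789 | 0.739 | 0.666 |
| 0.3 | 0.805 | 0.788 | 0.762 | 0.718 |
| 0.5 | 0.800 | 0.791 | 0.777 | 0.752 |
| 0.7 | 0.799 | 0.795 | 0.788 | 0.776 |
| 0.9 | 0.799 | 0.798 | 0.797 | 0.793 |

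At the counts used for the clip total, the extra preterm measurements offset the missing term ones. Power drops by more than about one percentage point only if preterm infants average about three sticks or fewer, and the drop is material only when ρ is low.

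**The case against.** A reader might infer that the study cannot deliver the power it claims. The article does not support that. The only explicit per-infant count for preterm infants is five, and with five and two the model returns 80–82%. Nothing in the article says that preterm infants are expected to average three or fewer, and the 67% figure needs every infant at the permitted minimum together with low correlation. All of these figures come from an assumed model set to 80%, not from an error in the article's own sums. This objection stands.

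A reader might also take the printed beta as evidence of a design with 20% power. That is not credible: 0.80 is the conventional value for power, and swapping the two labels is a common slip. It still needs correcting.

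Three narrower limits also stand. The eligibility text asks for at least two samplings in term infants, so two is the planned number in the abstract and clip count rather than a cap stated everywhere. Term infants hold about half of the GA information, not most of it. The baseline wording is ambiguous, so it cannot be asserted that the wrong quantity was sized.

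Finally, the GA association is one hypothesis among several aims, which also cover factor structure, interrater reliability, concurrent validity, sensitivity and specificity. The objection does not remove the contradiction between the stated numbers of heel sticks, which are all printed and are not details left to a fuller document.

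**Conclusion.** The concern holds as an inconsistency in the sample-size justification. The premise of three or more heel sticks per infant conflicts with the two planned for term infants and is not guaranteed for preterm infants, and the beta label is wrong as printed. Both defects are certain.

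A loss of power is possible but not proven. Under the assumptions above, power ranges from 67% (two sticks for all, ρ = 0.1) to 82% (five and two, ρ = 0.1), and it stays at about 80% at the counts used for the clip total. The true figure depends on the distribution of preterm heel sticks and on a within-infant correlation that the article does not give. This calls for correction and restatement and gives no ground for judging the study too small.

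**What to change.** - In Sample size and power, write power 0.80 (beta 0.20).
- Reconcile the number of measurements per infant across the abstract, the eligibility criteria, the data collection section and the sample-size paragraph.
- Rerun the power for N = 150 with two measurements for term infants and the expected two-to-five distribution for preterm infants, using the n = 23 and n = 71 data already cited. Restate the result with the effect size, variance components and sidedness behind it.
- Say whether baseline means the phase before the stick or the first heel-stick occasions.
- Describe 2106 clips as the maximum, with 900 if every infant has two heel sticks.

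The cost is one rerun on existing data and some rewording. Correcting the statement needs no extra infants. The downside is that the restated power may be slightly lower than 80%.

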## Discussion

The BPSN is already widely used in clinical settings in the German speaking areas of Europe. Pain assessment with the BPSN requires only two to three minutes of observation. Despite its practical application, another advantage of the BPSN is its consideration of various aspects of behavioral pain responses. Because of less intense facial reactions in premature neonates and the frequent presence of artificial respiration in this patient population, the consideration of various behavioral indicators of pain may provide further information for appropriate pain assessment. In addition, the repeated measurement design in this study will facilitate consideration of the development of pain responses across time.

The validation of the BPSN on a large sample of neonates with different gestational age and the consideration of the influence of individual contextual factors on pain reactivity should lead to a higher accuracy of routine pain assessment. A revised version of the BPSN may help the clinical staff to prevent and minimize the pain endured by neonates, particularly preterm neonates in NICUs. For preterm infants requiring intensive care, appropriate and efficient pain management is an important factor in later motor and cognitive development. This study will hopefully contribute to a more accurate pain assessment tool and to the prevention of negative long-term outcomes in this vulnerable patient population.

## Abbreviations

BPSN: Bernese Pain Scale for Neonates
GA: Gestational age
NICU: Neonatal intensive care unit
PIPP-R: Premature Infant Pain Profile-Revised
